**Overall**						
			Nominal	Binary	Number retained in each group	Risk ratio
			Ordinal	Binary	Change in composite adherence measure	Risk ratio

^a^PRD: pharmacy refill data.

^b^VAS: visual analog scale.

^c^OI: opportunistic infection.

^d^AFB: acid-fast bacilli.

^e^QoL: quality of life.

#### Secondary Outcomes

The secondary endpoints shall comprise clinical (weight and BMI), biological (viral load and AFB diagnosis), quality of life (measured with the self-functioning–12 quality of life assessment form), and all-cause mortality. Treatment discontinuation, reasons for discontinuation, and risk factors of treatment discontinuation shall also be determined. The trial endpoints are summarized in Table 1.

### Duration

The trial shall run for 6 months. Outcome assessments will be conducted at baseline, 2 months, 4 months, and 6 months.

### Sample Size Determination

The sample size determination is based on the test of the null hypothesis that the rates of adherence to ART in the intervention and control groups are equal. The primary measure of effect is the rate of adherence to ART as measured by using the VAS over 6 months. Given the information from previous studies [10,11], it is estimated that approximately 60% of participants would maintain adherence ≥95% without intervention and that the interventions would help 82% of the participants maintain ≥95% adherence. A two-sided test is assumed where an effect in either direction will be interpreted at a significance level of 5%. The study will have a power of 80% to yield a statistically significant result using a chi-square test (assuming an intention-to-treat principle for the analysis) of the relative risk at an alpha level of 5% to detect a 25% difference (60% vs 85%).

The formula for calculating the sample size for randomized controlled trials by Chan [26] is used.

where c=7.9 for 80% power and p1 and p2 are the proportion estimates (60% for the control group and 85% for the intervention group).

[figure not shown]

It is assumed that 10% of the participants shall drop out of the study due to loss to follow-up and mortality. A total of 52 participants shall be randomized to each arm to allow for the 10% drop out. Therefore, the required sample size will be 156 (52 x 3 = 156) participants.

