### Study Objectives

#### Primary Objective

The main aim of this trial is to investigate the impact of adding mobile phone SMS to the usual standard of care versus usual standard of care alone in improving retention in care and promoting adherence to treatment among HIV clients on treatment at 2, 4, and 6 months. Retention in care shall be defined as the proportion of clients who had started on ART, enrolled in the study, and attended clinic visits at the second, fourth, or sixth months. There is no gold standard in the measurement of adherence because the majority of the tools currently used cannot meet all the features of an ideal tool [25]. However, a multi-method tool is recommended and can include self-report and different combinations of other tools including pill count, the pill identification test (PIT) and visual analog scale (VAS), electronic methods, and drug levels. Therefore, a composite adherence measure shall be used in this study to reduce the errors associated with using a single adherence measure [25]. The adherence score shall be built on four adherence measures including a self-report questionnaire with 4 items, supplement of pill pick up from pharmacy refill records, a PIT consisting of 5 items, and a 30-day VAS. Adherence shall first be estimated by each measure and classified into three categories as high, moderate, and low before finally combining the results of the four measures into the composite adherence score.

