### Outcome Measures

#### Primary outcomes

The primary outcomes will be retention in care and adherence to treatments, measured using self-reports (supplemented by PIT, pharmacy refill data, and VAS; Table 1).

**Table 1 table1:** Overview of outcome measures.

Outcome measures			Scale	Type	Measure	Analysis method

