	**Adherence at baseline and at 2, 4, and 6 months**					
		Self-report	Ordinal	Binary	% adherence in last month >95%	Risk ratio
		Pill identification test	Ordinal	Binary	% of pills identified >95%	Risk ratio
		PRD^a^	Ordinal	Binary	% of complete refills >95%	Risk ratio
		VAS^b^	Ordinal	Binary	VAS percentage >95%	Risk ratio

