### Analysis Plan

The CONSORT (Consolidated Standards of Reporting Trials) guidelines will be used in reporting the results. The biostatistician shall be blinded to the group allocation. The process of client selection and flow throughout the study will be summarized using a flow diagram. The analysis of client demographics and outcome variables shall be summarized using descriptive summary measures, expressed as mean (standard deviation) or median (range) for continuous variables and number (percentages) for categorical variables. All outcomes shall be analyzed using an intention-to-treat principle where data from participants shall be analyzed according to the group to which they were randomized even if they do not receive the allocated intervention. Missing data shall be handled using the multiple-imputation method. The student *t* test and analysis of variance for comparing group means will be used. All statistical tests shall be performed using two-sided tests at the 5% level of significance. The Bonferroni method shall be used to adjust the level of significance for testing of secondary outcomes to keep the overall level at an alpha of 5%. For all group comparisons, the results shall be expressed as an effect (or risk ratio for binary outcomes), corresponding two-sided 95% confidence intervals, and associated *P* values. *P* values shall be reported to three decimal places with values less than .001 reported as <.001. Adjusted analyses using baseline variables shall be performed using regression techniques to determine the continuing influence of key baseline characteristics on the outcomes. The Kaplan-Meier survival analysis will be used for timed variables like mortality. All analyses will be performed using SPSS version 25.0 (IBM Corp) for Windows. Adherence will be measured both as a continuous outcome (change in adherence) and as a binary outcome (ie, adherent, 95% of pills taken, or nonadherent, <95% of pills taken) following the composite adherence score method. Adherence data shall be handled in a number of ways, reported as the number of doses respected, and shall be combined into a composite score. The effects of the intervention shall be reported on all the measures of adherence used and will be compared for discrepancies.

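### The primary adherence endpoint is named inconsistently across the article, so the stated power belongs to only one of several candidate endpoints

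*Protocol article*

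**What the plan says.** The protocol article describes the primary adherence endpoint in five places.

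- **Sample Size Determination:** "The primary measure of effect is the rate of adherence to ART as measured by using the VAS over 6 months". Rates are given for reaching ≥95%, and the formula uses 60% for control and 85% for intervention.
- **Outcome Measures, Primary outcomes:** adherence is "measured using self-reports (supplemented by PIT, pharmacy refill data, and VAS".
- **Study Objectives, Primary Objective:** "a composite adherence measure shall be used in this study to reduce the errors associated with using a single adherence measure". Each of the four tools is first "classified into three categories as high, moderate, and low before finally combining the results of the four measures into the composite adherence score".
- **Table 1:** the Primary block has separate binary rows for self-report, pill identification, refill data and VAS, each at baseline and months 2, 4 and 6, each above 95% and each with a risk ratio. The VAS row reads "VAS percentage >95" (per cent). The composite is not in this block. It appears under Overall as "Change in composite adherence measure", typed binary with a risk ratio.
- **Analysis Plan:** "Adherence will be measured both as a continuous outcome (change in adherence) and as a binary outcome", following the composite method, with below 95% counted as nonadherent. Effects on all adherence measures are to be reported and compared. The Bonferroni adjustment is given for secondary outcomes only.

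Retention in care is the other primary outcome and is not in dispute here.

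**The concern.** A sample size protects a conclusion only if the endpoint tested is the one that was sized. Here the sizing section rests on a single instrument. The Primary Objective argues against relying on a single instrument, and the Primary outcomes paragraph places the sizing instrument among the supplements. An analyst could follow any one of these sections and breach another.

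Two things are at stake. First, the 80% power is justified for one endpoint and may be read as applying to whichever is analysed. Second, if the adherence measures disagree, nothing says which one decides whether the intervention worked.

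This is not detail that an article may leave to an analysis plan. The article does define the endpoint, several times and in ways that conflict, so an analysis plan could agree with one section only by departing from another.

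**Working it through.** **1. The plan's own figure.** Inputs from Sample Size Determination: c = 7.9, p1 = 0.60, p2 = 0.85, 10% dropout. The formula image is not shown, so the usual form is assumed:

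n = c[p1(1−p1) + p2(1−p2)]/(p1−p2)² = 7.9 × (0.24 + 0.1275)/0.0625 = 46.45, so 47 per arm.

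Dropout: 46.45/0.9 = 51.6, so 52 per arm and 3 × 52 = 156. The stated size reproduces for one binary endpoint at 60% versus 85%. (The same section also mentions 82% for the intervention arms. That is a separate inconsistency; 85% is used here because the formula uses it.)

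**2. Does the power carry over?** The article gives no expected rates for self-report, pill identification, refill data or the composite, so power for those cannot be computed from it. To show the sensitivity, rates are assumed, with 52 × 0.9 ≈ 47 evaluable per arm and a two-sided 5% test:

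power = Φ{[|p1−p2|√n − 1.96√(2p̄(1−p̄))]/√[p1(1−p1)+p2(1−p2)]}, with p̄ the mean of p1 and p2.

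| Control vs intervention | Power |
|---|---|
| 60% vs 85% (plan) | 78% |
| 70% vs 95% (assumed) | 90% |
| 40% vs 65% (assumed) | 69% |
| 40% vs 56.7% (assumed, same risk ratio of 1.42) | 36% |
| 60% vs 75% (assumed) | 34% |

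A different endpoint can move power a long way in either direction.

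**3. The descriptions side by side.**

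- Measure: VAS (sizing); self-report with supplements (Primary outcomes); composite (Primary Objective, Analysis Plan); four parallel measures (Table 1).
- Cut-off: ≥95% in the sizing section, and exactly 95% counts as adherent in the Analysis Plan; Table 1 requires more than 95%.
- Time: over 6 months in the sizing section; months 2, 4 and 6 in the objective and Table 1. No visit is named as the primary one.
- Form: binary in the sizing section and Table 1; both continuous change and binary in the Analysis Plan. No rule turns the combined component grades into adherent or nonadherent, and none turns the change in the composite into a binary result.

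**4. Change scores.** Table 1 plans t tests on change for weight, BMI and quality of life. With equal variances at baseline and follow-up and correlation r between them, the variance of the baseline-adjusted comparison relative to the change-score comparison is (1−r²)/[2(1−r)] = (1+r)/2. The reduction is (1−r)/2: 25% at an assumed r of 0.5 and 15% at 0.7.

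**The case against.** The best defence is that the Analysis Plan commits to reporting every adherence measure and comparing them for discrepancies, which limits selective reporting. That stands. It does not settle which result is decisive, and the stated multiplicity adjustment does not reach the primary measures. The Primary outcomes sentence can also be read as a loose description of the composite. Even so, the sizing section and the Primary block of Table 1 would still disagree with it.

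Several stronger readings are tempting, but the article does not support them:

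- A reader might infer that the 60% and 85% rates apply to the VAS alone. The sentence giving the estimated rates names no instrument; only the sentence before it names the VAS.
- A reader might count five measures at three visits and say that one of 15 results was sized. The sizing section names no visit, so no single one can be identified.
- A reader might call the composite three-level. The three grades apply to each component, and the number of composite levels is not stated.
- A reader might say that a change can have no risk ratio. A binary change, such as improved or not, could have one; what is missing is the rule.
- A reader might see a contradiction between a 30-day VAS and a 6-month period. Repeated 30-day assessments can cover 6 months; only the decisive visit is unclear.
- A reader might argue that >95% leaves only a perfect score on the VAS or the five-item pill test. That depends on scoring steps that the article does not give.

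**Conclusion.** The concern holds in this form: the article names the primary adherence endpoint inconsistently in measure, cut-off, visit and form, and designates none as decisive. The power of 80% with 52 per arm is stated for one binary endpoint at 60% versus 85%, linked to the VAS, and does not automatically carry over to the others. The loss or gain for another measure cannot be computed from the article. The 34% to 90% range rests on assumed rates and shows sensitivity only. The differing cut-off is a small but real slip; its effect depends on how many participants score exactly 95%, which is unknown. The article does not show that a result was or will be selected after the fact, only that its text would not prevent it. Because a primary endpoint is affected, this must be settled before treatment groups are compared.

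**What to change.** Issue a dated amendment before unblinding. Allocation is complete and the article reports data collection and analysis as ongoing, so an undated choice would look post hoc.

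- Keep retention in care as a primary outcome.
- Name one primary adherence endpoint, with its measure, cut-off and visit. The simplest is 30-day VAS ≥95% at month 6. It keeps the sizing measure and cut-off; the visit is a new specification.
- If the composite is preferred, which is equally coherent given the reason in the Primary Objective, state its binary rule and re-justify the power on its own assumed rates. With 160 participants already allocated, that means stating the power available.
- Use ≥95% throughout, including Table 1.
- Label the remaining adherence measures as supportive and still report them all.
- Replace the Table 1 row pairing change in the composite with a risk ratio by the composite level at the chosen visit, adjusted for baseline.
- As a free improvement, analyse weight, BMI and quality of life by regression on the follow-up value adjusted for the baseline value already collected, in place of t tests on change.

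The cost is wording, Table 1 edits and the amendment itself, with no new data. If the VAS is chosen, the composite loses primary status and the single-measure error that the Primary Objective wanted to avoid is accepted.

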### Study Design

The design rests on a three-arm, randomized controlled trial with two intervention arms and one control group. The trial shall be single-blinded where the investigators and participants shall not be blinded to the intervention, whereas interviewers and data analysts will be blinded to group allocation. The intervention shall include the use of mobile cellphone SMS in addition to the standard of care provided to the clients. Participants shall be randomly allocated in a 1:1:1 ratio to one of three arms prior to the beginning of the intervention: (1) once weekly mobile phone SMS, (2) twice weekly mobile phone SMS, and (3) a control group that shall not receive mobile cellphone SMS. Clients will be recruited from the government-approved centers of the Regional Hospital Buea and Regional Hospital Limbe providing HIV treatment services.

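### The sample size paragraph gives two adherence rates for the SMS arms, 82% and 85%; the 52 per arm and the 80% power rest on 85%, and per-arm power would be about 66-68% if 82% is the expected rate

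*Protocol article*

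**What the plan says.** All the inputs but the allocation ratio stand in the Sample Size Determination section of the protocol article.

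- **Expected rates.** Citing two earlier studies, the section estimates that "approximately 60% of participants would maintain adherence ≥95% without intervention" and that "the interventions would help 82% of the participants maintain ≥95% adherence". That is a difference of 22 percentage points.
- **Power statement.** "The study will have a power of 80% to yield a statistically significant result using a chi-square test", two-sided at 5%, "to detect a 25% difference (60% vs 85"%). That is a difference of 25 points.
- **Formula inputs.** "where c=7.9 for 80% power and p1 and p2 are the proportion estimates (60% for the control group and 85% for the intervention group").
- **Result.** With 10% dropout allowed for, 52 participants are to be randomised per arm, 156 over three arms.

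The Study Design section sets the allocation: "Participants shall be randomly allocated in a 1:1:1 ratio to one of three arms". The Results section reports that 160 were actually randomised: 52 once weekly, 55 twice weekly and 53 control.

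**The concern.** One parameter, the proportion adherent in an SMS arm, has two values within one paragraph. The first is tied to earlier evidence. The second, which is larger, enters the formula with no source and no explanation. Both stand in running prose and 85% appears twice, so this is not a fault of text extraction. Nor is it a detail that a fuller document could supply, because the text commits to two incompatible numbers.

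The section names adherence on the visual analog scale as the primary measure of effect and gives no other basis for the trial's size. A reader who takes 82% as the expected rate and also accepts 80% power will think the trial better able to detect that effect than it is. A non-significant comparison of one SMS arm with control could then be read as stronger evidence against SMS than it would be.

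**Working it through.** **Inputs.** Control rate 0.60; SMS rate 0.82 or 0.85; c = 7.9; two-sided 5% chi-square test; 10% dropout; 52 randomised per arm. The formula itself is a figure that is not shown. I assume the usual form that fits the stated inputs:

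n per arm = c × [p1(1 − p1) + p2(1 − p2)] / (p1 − p2)²

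**Step 1: reproduce the plan's figure with 85%.**

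n = 7.9 × (0.60 × 0.40 + 0.85 × 0.15) / 0.25² = 7.9 × 0.3675 / 0.0625 = 46.45, so 47 evaluable.

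Dropout: 46.45 / 0.9 = 51.6, so 52 per arm, and 3 × 52 = 156. The plan's figures reproduce.

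**Step 2: the same formula with 82%.**

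n = 7.9 × (0.60 × 0.40 + 0.82 × 0.18) / 0.22² = 7.9 × 0.3876 / 0.0484 = 63.27, so 64 evaluable.

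Dropout: 64 × 1.1 = 70.4, so 71, or 64 / 0.9 = 71.1, so 72 per arm. The total would be 213 to 216, against 156.

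**Step 3: power for one SMS arm against control.** 52 less 10% is 46.8, taken as 47. With d = p2 − p1, p̄ the mean of p1 and p2, SE1 = √{[p1(1 − p1) + p2(1 − p2)]/n} and SE0 = √{2p̄(1 − p̄)/n}:

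- unpooled: Φ(d/SE1 − 1.96)
- pooled: Φ((d − 1.96 × SE0)/SE1)
- exact: enumeration of the uncorrected chi-square test

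For 60% versus 82% and n = 47, SE1 = √(0.3876/47) = 0.0908 and SE0 = √(2 × 0.71 × 0.29/47) = 0.0936.

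- Unpooled: Φ(0.22/0.0908 − 1.96) = Φ(0.463) = 67.8%
- Pooled: Φ((0.22 − 1.96 × 0.0936)/0.0908) = Φ(0.402) = 65.6%

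| Effect | n per arm | Pooled | Unpooled | Exact |
|---|---|---|---|---|
| 60% vs 85% | 47 | 78.4% | 80.7% | 79.3% |
| 60% vs 82% | 47 | 65.6% | 67.8% | 66.6% |
| 60% vs 82% | 52 | 70.1% | 72.2% | 71.3% |

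**Step 4: numbers actually randomised.** For the larger SMS arm, 55 against 53 controls with nobody lost, power at 60% versus 82% is 71.9% pooled, 73.6% unpooled and 73.1% exact. The extra enrolment does not close the gap.

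**Step 5: chance of missing the effect, same method on both sides, 47 per arm.** At 82% against 85%: 34.4% against 21.6% (pooled), 33.4% against 20.7% (exact), 32.2% against 19.3% (unpooled).

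**The case against.** Three points can be made for the plan.

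**The 80% is claimed only for 60% versus 85%.** This stands. At 47 per arm the power for that effect is 78-81%, so the calculation is sound for the effect it names. A reader might infer that the stated power is simply false, or that the trial has 66% power. The document supports neither, because it never claims 80% power at 82%.

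**The 82% may be a slip for 85%.** This also stands as a possibility. The 85% appears twice, agrees with the stated 25-point difference and drives the formula, while 82% appears once. Against that, 82% is the figure introduced with the earlier studies. Those studies are not at hand, so the question cannot be settled here. If 82% is a slip, there is no power shortfall and the correction is a single number. Every statement about lower power is therefore conditional on 82% being intended.

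**Combining both SMS arms against control would restore the power.** A reader might infer this from the general wording of the objectives, which speak of SMS versus usual care. For 94 against 47 at 60% versus 82%, power is 77-80% depending on the method (76.8% unpooled, 79.6% pooled, 79.8% exact). But the plan does not explicitly specify a combined-arm test, and its calculation sizes each arm with a two-group formula and multiplies by three. Singling out that contrast now, after recruitment, because its power is favourable would not be sound.

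Intention-to-treat with multiple imputation, which the Analysis Plan calls for, moves the 82% figure towards 70-72%. That is an upper bound, since imputation does not fully recover lost information. The planned 95% confidence intervals also limit the risk of misreading a null result.

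**Conclusion.** The contradiction is certain: 82% and 85% are both given for the SMS rate, and nothing in the document reconciles them. The 52 per arm and the 80% power belong to 85%.

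The consequence depends on which rate is meant. If it is 85%, the sizing stands. If it is 82%, a test of one SMS arm against control falls 12-14 points short of 80% after the planned dropout, and 8-10 points short if all 52 are analysed. The chance of missing the effect is then about 32-34%, against 19-22% at 85% on the same methods. The shortfall appears under every method tried, with planned and with actual numbers.

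These figures assume the inferred form of the formula, an uncorrected two-sided 5% chi-square test, and one SMS arm compared with control.

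**What to change.** Keep the enrolled number. In Sample Size Determination, reconcile the two rates and say which is the evidence-based expectation.

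- **If 85% is intended:** correct the 82% and make sure the earlier studies cited support 85%. The sample size and power statement stay as they are.
- **If 82% is intended:** keep 60% versus 85% only as the effect the trial was sized to detect. Add that per-arm power at 60% versus 82% is about 66-68% after 10% dropout, and 70-72% if all 52 per arm are analysed.

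In neither case should a combined SMS-versus-control comparison be put forward as the one with 80% power.

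The cost is a few sentences. No participants, tests or analysis sets change. In the second case the stated per-arm power becomes less favourable. The article says analysis is still under way, so the correction should be made before the results are interpreted.
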